Two recent meta-analysis [26, 28] have assessed the effect of parental interactive book sharing on 1- to 6-year-old children’s language gain in randomized controlled studies (RCT) studies. Both studies corroborate the conclusion of the efficacy of interactive book sharing for children’s vocabulary development. The study by Dowdall et al. [26] reported small sized effects on expressive (*d* = .41, CI = .20, .61) and receptive (*d* = .26, CI = .12, .40) vocabulary, but larger effects were found for studies with medium to high intervention dose (i.e., more than 60 min contact time). This meta-analysis also showed a large sized intervention effects on caregiver book sharing competence (*d* = 1.01, CI = .40, 1.63), such as “caregiver expansion during book sharing,” “parental sensitivity and reciprocity during book sharing,” and “caregiver use of an interactive reading style.” However, one important caveat is that only five of the 19 studies included in the meta-analysis provided such data and these studies were limited due to small sample sizes and/or absence of an active control group. It was further reported that group-based interventions were associated with greater intervention gains in language compared to one-on-one interventions. Although speculative, the latter finding could indicate that the group-based format offered more learning opportunities through participant sharing their experiences or through increased social support [26]. Another possibility is that the group format increased participant adherence to the intervention protocol. This finding also points to the importance of using an adequately designed active control group instead of a no-contact (wait-list) group to control for nonspecific intervention effects, such as effects of increased social support in group interventions.

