### Intervention

#### Index group

The intervention was a group-based book sharing program for caregivers, “the Mikhulu Trust book sharing programme for children aged 10–24 months” (www.mikhulutrust.org). The program structure and content has been informed by the original Whitehurst model [39, 40]. The program has previously been evaluated with children aged 14–18 months [37, 39, 40]. It was adapted for the targeted age-group by selecting age-appropriate picture-books and by focusing on teaching caregivers’ book sharing techniques most relevant for when sharing books with infants. The intervention program was delivered by a trained facilitator weekly for five consecutive weeks to groups of around 4–6 parent-child dyads. Each session (60 min) was organized around specific topics and incremental techniques; see Table 1 for a description of the content for each session. During each session, the caregivers sat in a semicircle facing the facilitator. Sessions 2 to 5 began with a review wherein the participating caregivers shared and discussed their experiences of book sharing in the preceding week, with the guidance of the facilitator. In each session, key learning points were presented to caregivers through PowerPoint slides. The slides included instructive pictures and video clips to demonstrate the key techniques to apply during book sharing with their child. The caregivers were encouraged to be involved in the session by expressing their opinions and by asking questions about the session content. During this part of the session, toys were available on the floor for the children to explore.

**Table 1 Tab1:** Intervention sessions

Session	Session content
1	**Introduction and getting started** (using “Vi går på Babyrytmik” by Moa Eriksson Sandberg & Erik Sandberg). The benefits of book sharing to children’s development are presented. The key principles of book sharing are introduced and the caregiver is encouraged to engage the child actively with the book, to facilitate the child’s handling of the book, to help the child to turn pages and steady the book, to follow the child’s cues and interest, to praise the child, to have fun together, and to support their child. The importance of establishing a book sharing routine is emphasized.

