#### Active control group

The active control group sessions were designed to mimic the sessions of the index group in important ways. The purpose of the active control group was to ensure that any potential intervention effects related to book sharing training were not due to being part of a professionally managed social group or because of receiving more professional attention from researchers. The participants (parent-child dyads) in the active control group attended group sessions for the same amount of time as the index group. They met weekly for five consecutive weeks in groups of around 4–6 parent-child dyads. The group sessions were held at different locations, but each group always met at the same time and at the same location. To control for the potential effect of location, every control group met at the same location as one index group during the same week but at a different time point (e.g., a control group meet in the morning and an index group in the afternoon). The order of the group meetings (index or active control first) was randomized between paired index-control groups prior to the start of the study. The active control group sessions and intervention sessions were held by the same facilitator.

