### Sample size

The originally targeted sample size was 140 children (10-month-old ± 4 weeks) and their caregivers (70 dyads in each arm). The sample size was calculated on the basis of the primary outcome measure language. The power calculation was conducted in G*Power [55] using 80% power and alpha set to = .05. The effect size (*d*) for the power calculation was based on the results reported in a recent meta-analysis by Dowdall et al. [26]. The meta-analysis [26] was based on RCT book sharing interventions targeting young children (1 to 6 years) and reported an overall effect size of *d* = .54 for expressive language in studies using medium to high intensity intervention dose (i.e., more than 60 min contact time). Based on this estimate, an index and control sample of 55 dyads in each arm would therefore be sufficient to detect a difference (two-tailed) and would allow for an attrition rate > 10%. The study’s final sample size was 115 parent-child dyads (index group, *n* = 59; active control group, *n* = 56). Thus, the study’s sample size is sufficiently powered.

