### Statistical methods

All statistical analysis will be conducted using the SPSS and R software. Data will be screened to check for data entry errors and to test if the data meet the assumptions of parametric procedures. The pattern and amount of missing data will be examined and handled by using maximum-likelihood estimates (or similar estimates), if appropriate. Baseline data and demographic characteristics will be described using summary statistics (means and standard deviations or number and percentages). Group baseline differences will be assessed using independent samples *t* test, chi-squared test, and Mann-Whitney *U* test. Fidelity in terms of adherence and the dose of the intervention will be summarized using descriptive statistics. All tests will be two-sided and 5% will be used as the level of significance. Effect size measures (e.g., Cohen’s *d*) will be calculated to describe intervention effects.

The statistical analyses of the primary outcomes will be performed blinded to treatment allocation. In accordance with CONSORT guidelines, intention-to-treat principles will be used to prevent systematic bias. Linear mixed models or analysis of covariance will be used to assess intervention effects at post intervention and at the follow-ups. Baseline scores will we controlled for as covariates. Other potential covariates (e.g., child monolingual status) will be investigated by examining correlations between covariates and the outcome variables.

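### Both arms are delivered in fixed groups of about 4–6 dyads, but the sample size assumes independent dyads and the analysis permits an ANCOVA with no delivery-group term

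*Protocol article*

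**What the plan says.** **Delivery.** Under Index group, the protocol article says the programme was "delivered by a trained facilitator weekly for five consecutive weeks to groups of around 4–6 parent-child dyads". Under Active control group it gives the same group size and duration, says that each group kept its own time and place, and adds that "every control group met at the same location as one index group during the same week but at a different time point". The same facilitator ran the sessions in both arms. From the second session on, participants in both arms discussed the past week together.

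**Randomisation.** Objectives and Sequence generation describe allocation of individual dyads, 1:1 in blocks. This is therefore an individually randomised trial with group-delivered treatment in both arms. It is not a cluster-randomised trial.

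**Sample size.** "The power calculation was conducted in G*Power [55] using 80% power and alpha set to = .05". The effect comes from a meta-analysis that "reported an overall effect size of *d* = .54 for expressive language" at medium to high dose. The section arrives at 55 dyads per arm, two-tailed, and then states "The study’s final sample size was 115 parent-child dyads" (59 index, 56 control) and concludes that power is adequate. It mentions no ICC or design effect.

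**Analysis.** Statistical methods says "Linear mixed models or analysis of covariance will be used to assess intervention effects at post intervention and at the follow-ups". Baseline scores are covariates, and others, such as monolingual status, may be added after their correlation with outcome is examined. Delivery group and the location-week pairing are not mentioned.

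**The concern.** Dyads who spend five weeks with the same few families, discussing and practising together, may end up with outcomes more alike than those of dyads in different groups. Each delivery group belongs wholly to one arm, so variation specific to a group adds directly to the variance of the arm difference. A method that takes dyads as independent leaves that part out.

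ANCOVA is offered as an equal alternative to the mixed model. An analyst could follow the text exactly and never account for group. If group-specific correlation is positive, confidence intervals would then be too narrow and the two-sided 5% level would not be kept. The statement that the trial is adequately powered also rests on an independence assumption that the article does not acknowledge.

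**Working it through.** **Inputs from the article.** Two-sided alpha 0.05, power 80%, d = 0.54, 55 per arm (Sample size); 115 dyads at baseline and 109 at post-assessment (Recruitment); groups of about 4–6 (Index group, Active control group).

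**Assumptions.** Group size m = 5, the middle of the stated range, which gives 115/5 = 23 groups, or about 22 for 109 dyads. The ICC is not given, so 0.01, 0.05 and 0.10 are used. The 109 are split 56/53, since the article gives only the total.

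**Step 1: reproduce the stated figure.** A two-sample t test (noncentral t) needs 54.81 per arm, rounded up to 55. Power is 79.4% with 54 per arm and 80.1% with 55. The published figure is thus the independent-dyads answer, with a design effect of 1.

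**Step 2: design effect and type I error when group is ignored.** DE = 1 + (m − 1) × ICC; the true standard error is √DE times the reported one; type I error = 2[1 − Φ(1.96/√DE)].

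| Assumed group-specific ICC | DE | √DE | Type I error |
|---|---|---|---|
| 0.01 | 1.04 | 1.020 | 5.5% |
| 0.05 | 1.20 | 1.095 | 7.4% |
| 0.10 | 1.40 | 1.183 | 9.8% |

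**Step 3: unadjusted power for d = 0.54.** Noncentrality = 0.54/√[(1/56 + 1/53) × DE]. With DE = 1 this is 0.54/0.1916 = 2.82, and power is 79.7%.

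| ICC | Noncentrality | Power, 109 dyads | Same, with 22 − 2 = 20 df | Needed per arm (54.81 × DE) |
|---|---|---|---|---|
| 0.01 | 2.76 | 78% | 75% | 58 (57.003 rounded up) |
| 0.05 | 2.57 | 72% | 69% | 66 |
| 0.10 | 2.38 | 66% | 62% | 77 |

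**Step 4: effect of the pairing.** Correlation shared by an index group and its paired control group cancels from the arm contrast. Write ρg for the group-specific part and ρp for the pair-shared part. The ratio of true to assumed variance is then about 1 + (m − 1)ρg − ρp. At a total ICC of 0.05:

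- none shared: 1 + 4(0.05) = 1.20, type I error 7.4%;
- half shared: 1 + 4(0.025) − 0.025 = 1.075, 5.9%;
- 80% shared: 1 + 4(0.01) − 0.04 = 1.00, 5.0%.

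A simulation of 11 pairs of groups of five gave 7.4%, 5.8% and 5.1%. The table in Step 2 therefore applies to group-specific correlation only.

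**Step 5: effect of baseline adjustment.** Suppose the baseline–outcome correlation is 0.5 (assumed) and d = 0.54 is on the raw-SD scale. The effective d becomes 0.54/√(1 − 0.25) = 0.624. Power with 109 dyads is then about 84% at ICC 0.05 and 78% at ICC 0.10, or about 81% and 74% with 20 df.

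**The case against.** Four stronger readings are tempting, and the article supports none of them.

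**That the mixed model ignores group.** The article does not say so. It leaves the random effects open, and a condensed article commonly leaves that detail to the full protocol or analysis plan, which are not shown. Nor does it adjust for baseline alone, since it allows for further covariates. What stands is that group is named nowhere and that ANCOVA, which as described has no place for it, is an equal option.

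**That standard errors are certainly too small.** This requires a positive group-specific ICC, and none is given. At 0.01 they are understated by only about 2%. The pairing by location and week, with a shared facilitator, can offset part of the inflation and, in Step 4, nearly all of it.

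**That the Background implies non-zero correlation.** It says "It was further reported that group-based interventions were associated with greater intervention gains in language compared to one-on-one interventions", which concerns a mean difference between formats. A shift common to all groups creates no correlation within them, and the article calls its peer-support explanation speculative. Equally, the active control removes a mean effect of meeting in a group; it does not remove correlation among members of one group. Clustering is plausible here but not established.

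**That 80% power is overstated.** The planned baseline adjustment could restore it (Step 5). What stands is that the claim of adequate power comes from a calculation with no allowance for clustering, and that unadjusted power with 109 dyads is already 79.7% before any is made.

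**Conclusion.** The point holds in conditional form. Both arms are delivered in stable small groups, the sample size assumes independent dyads, and the stated analysis permits a method that ignores group.

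With groups of five and assumed group-specific ICCs of 0.01 to 0.10, a test that ignores group has a true type I error of about 5.5% to 9.8% at a nominal 5%, and less where correlation is shared within location-week pairs. Unadjusted power with 109 dyads is about 78% to 66%, against 79.7% under independence. The ICC, the group size of five and the 56/53 split are assumptions. So is the baseline correlation that decides how much power is recovered.

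Because the size depends on an unknown ICC and the mixed-model option could already include group, this is a should-fix matter and not a demonstrated failure of the analysis.

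**What to change.** For confirmatory tests, specify a linear mixed model adjusted for baseline score, with a random intercept for delivery group in both arms, a location-week pair term (random, to limit the loss of degrees of freedom) and Satterthwaite or Kenward-Roger degrees of freedom. Do not use an ANCOVA that ignores group for these tests. In Sample size, state that 55 per arm assumes independent dyads, and show power over a range of ICCs.

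No new data should be needed: groups were fixed and attendance was recorded, so group membership should be recoverable. The article describes the 24-month follow-up as still under way, so for that assessment at least the model could be fixed before the data are complete.

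The cost is somewhat wider intervals and about 10–20 denominator degrees of freedom instead of about 107 (109 − 2): about 20 from 22 groups, or about 10 if arm is in effect tested within 11 pairs. The critical t rises from 1.98 to 2.09 or 2.23.

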*An EEG and eye tracking based mismatch-paradigm* [44] is used to assess child *word comprehension* at baseline and post-assessment. The child participants sit in front of 22″ monitor, with a Tobii X3-60 eye tracker attached to its bottom, while wearing a 128-channel Geodesics Sensor Nets. This task consists of 48 trials. Every trial starts out with displaying a scene consisting of a floor and a blue occluder on the monitor. A sentence with a word (“Look at X”) was presented over headphones to the caregiver who has been instructed to repeat the sentence to their child. Once the sentence is uttered, the experimenter pushes a button. Following this, the occluder disappear and an object (representing a common noun, e.g., a duck, a ball, or a car) is revealed. Objects are congruent (50%) or incongruent (50%) with the word spoken by the caregiver. This task has two outcome measures: (1) we measured an event-related brain potential known as the N400 (based on differential amplitude on congruent and incongruent trials, averaged across trials), and (2) we measure a pupil dilation difference score based on differential dilation on congruent and incongruent trials, baseline corrected and averaged across trials (see for example [45]). For both measures, the assumption is that if the child has developed a word knowledge of a specific word/object, they will detect the mismatch between presented word and object on incongruent trials. This mismatch is then reflected in enhanced N400 amplitude and increased pupil dilation on incongruent trials (vs congruent trials).

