#### Procedure

Data collection occurs at four time points: at baseline, following the 5-week intervention, and 6 and 12-months post intervention. At each time point, the participating caregiver complete a questionnaire using a secure online platform (https://sv.surveymonkey.com). Lab assessments take place at the first three assessment time points. Prior to each lab assessment, the child’s caregivers (legal guardians—when applicable) receive written information about the study purpose and procedures. Before each study visit, we collect written consent from the child’s caregivers. All participants are informed that that they have been given an anonymous identity number and that their data will be treated confidentially, that published reports of results from the study will be reported at a group level (meaning that it will not be possible to identify individuals), and that they can stop participating in the study at any time without giving any reasons. Participants are also informed that they have the right to have their data removed from the database at any time. During each study visit, the participating child’s caregiver is with the child at all time and can pause or stop data collection at any time. Similarly, the data collector pauses or stops the data collection during study visits if the child participant shows signs of discomfort or tiredness. Lab assessments last for up to 1.5 h, including breaks. The participants receive a gift card (€10) at each lab visit as a form of travel reimbursement.

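### With baseline as a covariate, a child with a usable post-intervention score but a failed baseline lab task drops out of that primary analysis as ordinarily fitted, and the missing-data sentence commits to no method that would keep the child

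*Protocol article*

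**What the plan says.** The Statistical methods section of the protocol article names two models for the intervention effect at post-intervention and follow-up, linear mixed models or analysis of covariance, and leaves the choice open. It fixes the role of baseline: "Baseline scores will we controlled for as covariates". On missing data it says: "The pattern and amount of missing data will be examined and handled by using maximum-likelihood estimates (or similar estimates), if appropriate". It also invokes intention-to-treat principles.

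Table 2 lists five lab-based primary measures with both a baseline (T1) and a post-intervention (T2) score: preferential looking, pupil dilation, N400, initiating joint attention and responding to joint attention. The looking task has 32 trials. Of the combined EEG and eye-tracking task the article says "This task consists of 48 trials", done under a 128-channel net. The two joint-attention tasks add 9 + 8 = 17 trials. Under Procedure, a lab visit lasts up to 1.5 h including breaks, and "the data collector pauses or stops the data collection during study visits if the child participant shows signs of discomfort or tiredness".

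Under Recruitment, 115 dyads completed baseline and 109 completed the post-assessment. No count of usable scores per task is given.

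**The concern.** A dyad can attend baseline, be counted among the 115, and still leave without a usable score on one or more tasks. The same child may give a good score at T2. In a model that conditions on baseline, that child has an outcome but no covariate value, and standard software removes the record.

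The baseline score is in the model mainly to gain precision. If requiring it removes children with valid outcomes, the adjustment can cost more precision than it brings. The loss would fall on the direct child measures, which are collected or coded by staff blind to allocation, and not on the vocabulary checklist, which is completed by parents who know their group. The analysed set would also shrink by a different amount for each measure, because of failures at baseline and not only at T2.

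**Working it through.** **Inputs from the article.** Sample size section: "The power calculation was conducted in G*Power [55] using 80% power and alpha set to = .05"; "reported an overall effect size of *d* = .54 for expressive language"; "an index and control sample of 55 dyads in each arm would therefore be sufficient to detect a difference (two-tailed"); "The study’s final sample size was 115 parent-child dyads (index group, *n* = 59; active control group, *n* = 56"). Recruitment section: 109 dyads at post-assessment.

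**Inputs assumed.** Task failure f = 10% to 40% at each visit, independent between visits unless stated; baseline-post correlation ρ = 0.2 or 0.5; near-equal arms among the 109 (56 + 53 in the simulation, since the article gives only the total). The value d = 0.54 belongs to expressive language, so its use for the lab measures is illustrative.

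**1. The plan's own figure.** The two-sided two-sample t test with d = 0.54 and 55 per arm has power 80.1% (noncentral t); the normal approximation gives 54 per arm. The stated 55 is reproduced. With 109 children and no adjustment, power is 79.8%, so there is little to spare.

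**2. Does the model drop the child?** A mixed model with baseline as a fixed covariate was fitted to 109 simulated children, 30 of them without a baseline. It used 79. Least-squares analysis of covariance does the same.

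**3. Children available.** Both scores: 109(1 − f)². Any T2 score: 109(1 − f).

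**4. Power.** Both formulas use the noncentral t.
- Complete cases: n = 109(1 − f)², noncentrality = [d/√(1 − ρ²)]·√(n/4), n − 3 degrees of freedom.
- All T2 scores, baseline used where present: n = 109(1 − f), residual variance about 1 − ρ²(1 − f), n − 4 degrees of freedom.

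Example, f = 10%, ρ = 0.2:
- Complete cases: n = 109 × 0.81 = 88.3; 0.54/√0.96 = 0.551; noncentrality 0.551 × √22.07 = 2.59; power 72.6%.
- All T2: n = 98.1; 0.54/√0.964 = 0.550; noncentrality 0.550 × √24.5 = 2.72; power 76.9%.

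Results for ρ = 0.2. The simulation used 4,000 runs per cell; its second arm is analysis of covariance with mean-imputed baseline and a missing indicator.

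| f | Both scores | Any T2 score | Formula: complete cases vs all T2 | Simulation: complete cases vs all T2 |
|---|---|---|---|---|
| 10% | 88 | 98 | 72.6% vs 76.9% | 73% vs 76% |
| 20% | 70 | 87 | 62.1% vs 71.7% | 62% vs 72% |
| 30% | 53 | 76 | 50.6% vs 65.6% | 50% vs 65% |
| 40% | 39 | 65 | 39.0% vs 58.5% | about 37% vs 57% |

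Repeat simulations agree within about two percentage points.

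**5. Sensitivity to the assumptions.** At ρ = 0.5 and f = 30%, simulated power is 60% vs 71%. If failures are correlated between visits (latent correlation 0.5), f = 30% and ρ = 0.2 give 55% vs 64%.

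**6. Does adjustment on complete cases beat no adjustment?** Unadjusted power on all T2 scores is 75.4%, 70.3%, 64.4% and 57.6% for f = 10% to 40%. At ρ = 0.2, complete-case adjustment is lower in every row above. At ρ = 0.5 it gives 82.5%, 72.8%, 60.8% and 47.7%: better at 10% and 20%, worse at 30% and 40%.

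**7. Do the alternatives recover the loss?** With ρ = 0.5, baseline missing at random in 40% and all T2 scores present, the standard error of the effect is 0.165 with full data, 0.213 for complete cases, 0.174 for joint likelihood of baseline and outcome, and 0.177 for mean-imputed baseline. Mean estimates in all settings run lay between 0.53 and 0.55 against a true 0.54, complete cases included.

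**The case against.** **The wording may already cover this.** A reader might infer that the plan excludes children without a baseline score and that its maximum likelihood cannot recover them. The article says neither. Its missing-data sentence is not limited to outcomes, and joint likelihood, an EM method or multiple imputation would all fit it and keep the child. This stands, and it limits the point to what the named models do as ordinarily fitted. But the sentence is qualified twice, by an allowance for similar estimates and by a condition of appropriateness, so it secures none of these methods.

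**The detail may be in an analysis plan that is not shown.** That is fair for the handling of missing covariates as such. The point here is about a choice the article does make, the role of baseline, for which a better and nearly free alternative exists.

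**Failure may be rare.** Collection may be paused instead of stopped, assessments can be rescheduled, and scores are averages or proportions across trials, so a shortened task need not mean a missing score. All of this stands. No failure rate is reported, and at 10% the loss is about 3 percentage points.

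**The outcome used for sizing is untouched.** Expressive language comes from an online parent questionnaire, so lab-task failure does not affect it. This is correct; the power figures for the lab measures are illustrative only.

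**The remedy has its own assumption.** A common baseline mean, or mean imputation across arms, supposes that baseline is unaffected by allocation. The Concealment mechanism section has allocation released before baseline, and 151 dyads were randomised but 115 completed baseline. Randomisation therefore does not by itself guarantee equal baselines among attenders. This stands and shapes the fix.

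**Conclusion.** The point holds in a limited form and is worth acting on. In the two models named, with baseline as a covariate and likelihood applied to the outcome alone, children with a T2 score but no T1 score on a lab task are lost, and the article commits to nothing that prevents it.

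The consequence is reduced precision on up to five primary measures. At ρ = 0.2 it ranges from about 3 percentage points of power at 10% failure per visit to about 20 points at 40%. These figures rest on assumed failure rates and correlations and on a borrowed effect size; the true loss could be negligible if nearly all baseline tasks succeed.

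Two stronger readings are not supported. A reader might infer bias: none is shown, since with failure unrelated to outcome the complete-case estimates were close to the true effect. A reader might also infer a contradiction with the intention-to-treat statement: the article does not say that such children are excluded, and the analysed set would vary by measure anyway whenever T2 tasks fail.

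**What to change.** Replace the sentence on baseline covariates with a rule for every primary measure that has a baseline: all children with a usable post-intervention score are analysed. Either of two routes achieves this.

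- Model the baseline and later scores jointly as outcomes (T1, T2, and T3 where measured), with a common baseline mean and arm-by-visit effects, as a constrained longitudinal mixed model or by joint maximum likelihood.
- Keep analysis of covariance, set a missing baseline to the overall baseline mean, and add a missing-baseline indicator.

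Choose one before allocation is revealed to the analysts. For each measure, report by arm how many children have T1 only, T2 only and both. Because allocation was released before baseline, check that baseline scores and baseline missingness are similar between arms, and keep complete-case analysis of covariance as a sensitivity analysis.

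The cost is a sentence or two in the analysis section, slightly more model code in SPSS or R, and reliance on the assumption that baseline is unaffected by allocation. No new data are needed.
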